### Intervention arms

#### Shamiri intervention

The Shamiri intervention consists of three modules: a growth-mindset module [17, 19, 31] lasting two sessions, a gratitude module [20] lasting one session, and a virtues module based on value affirmations [21, 32] lasting one session. More detailed information on these sessions is provided below.

##### Growth-mindset interventions

Growth-mindset interventions target implicit theories about the ability of human attributes to evolve over time. As such, growth-mindset interventions challenge the belief that personality traits and intelligence are fixed and unchangeable. These interventions are designed to strengthen individuals’ beliefs in the malleability of such characteristics [19, 33]. Meta-analyses of growth mindset interventions have shown robust improvements in academic achievement, particularly among low-income students [34].

##### Gratitude interventions

Research on trait gratitude suggests that grateful people exhibit more positive states and outcomes than non-grateful people. Gratitude interventions teach individuals to be more aware of and thankful for the positive people and things in their lives, regardless of whether they are tangible or not [20].

##### Value affirmations interventions

Value affirmation interventions invite people to reflect on specific values that are most important to them. This self-reflection can improve people’s coping skills by reestablishing an awareness of personal worth and integrity [21, 32]. Due to differences in language and vocabulary, the discussion of values will be presented to Kenyan youths as “virtues.”

#### Structure of intervention sessions

The intervention consists of four intervention sessions, which are each 1-h long and 1 week apart. All of the sessions include reading activities, group discussions, and writing activities. Homework exercises are assigned between sessions. In sessions one and two, participants learn about growth, neuroplasticity, and work to build their growth-mindsets. In sessions three and four, participants learn about gratitude and value affirmations respectively.

##### Session one: growth

In session one, the group leader begins with group introductions and an ice-breaker activity. Then, the group leader provides a didactic introduction to growth and personal improvement in different areas—social, academic, and emotional—and their benefits. Participants then read an article and watch a short video that explains neuroplasticity: a phenomenon whereby the brain grows and makes new connections as a result of learning and practicing new skills. Both the article and video script are available in supplementary materials; the video is available upon request and online. Next, the participants read three growth testimonials from local Kenyan peers and a growth testimonial from their own group leader (see supplementary materials). Testimonials focus on personal growth in a plethora of domains (e.g., school performance, personality, happiness, relationships). Participants then have a discussion about the testimonials. To conclude the first session, participants are assigned a take-home activity in which they identify a challenge they faced, describe how they used effortful strategies to deal with the challenge, and reflect on how they grew as a result of the challenge.

##### Session two: growth

In session two, participants begin by discussing their take-home activity. They then brainstorm and discuss effective strategies that they can use to apply the lessons of growth-mindset in their own lives. Next, the group leader will moderate a discussion about problem-solving skills modeled off of the problem-solving STEPS module [35]. Afterward, participants are instructed to write a letter to a friend in which they explain the concepts that they have learned thus far—including neuroplasticity, growth-mindset, effective strategies, and problem-solving skills—in their own words. The group leader is instructed to do all of the same activities themselves while the participants do them. Lastly, participants are assigned a take-home activity in which they think of one problem that currently affects them and brainstorm solutions modeled off the problem-solving skills learned in the session. They are encouraged to try one or more of these solutions during the week.

##### Session three: gratitude

In session three, students learn about gratitude. The group leader opens the session with a didactic introduction to gratitude and its various benefits. The participants then discuss gratitude and identify people and things for which they are grateful. After this, participants write a “gratitude letter” [36] to a living person who has changed their life for the better. For homework, participants are instructed to complete a daily “three good things” activity during the following week [37]. In this activity, participants identify and write three good things that happened each day and write a short reflection for each.

##### Session four: virtues

In session four, students learn about virtues and their importance in everyday life. While the activities in this section are based on empirically-tested value affirmations exercises, the discussion of values will be presented to Kenyan students as “virtues” due to differences in language and vocabulary. The group leader opens the session with a didactic introduction to what virtues are. The group then enters a discussion about virtues, noting why they are important in guiding daily behavior and helping us find purpose in our lives. Students are then asked to select from a long list several virtues that are meaningful to them. Next, students select the one particular virtue that they feel is most important to them and describe, in writing, why this virtue is important, a time when they have lived up to that virtue, and how they can live in better accord with this virtue in the future [21]. There is no take-home activity following this fourth and last session. At this point, participants are allowed to keep the Shamiri booklet, which contains all the lessons and exercises from the four sessions for both the Shamiri intervention and the control. Session four also last for 40 min to allow students ample time to complete endpoint assessment.

#### Study-skills control

Using a study skills control group both presents participants with an opportunity to benefit from participation and provides a more rigorous standard of comparison than passive controls [22].

The control condition consists of four modules: a note-taking module lasting one session, an effective-study-strategies module lasting one session, a time management module lasting one session, and a study cycle module lasting one session. All these modules were developed specifically for a pilot trial of the Shamiri intervention [13]. More information on these sessions is provided below:
*Note-taking*: Developing effective note-taking skills may help students improve their academic performance. The session will cover what the study team will present as the 5Rs of note-taking: Record, Reduce, Recite, Reflect, and Review (see online supplementary materials for more information).*Effective study strategies*: Effective study strategies may help students understand what they are learning and how they can optimize their time spent studying. The session will cover 10 effective study strategies compiled by the study team, including “have a study plan,” “don’t cram all studying into one session,” and “start with the most difficult subject” (see online supplementary materials for more information).*Time management*: Time management skills may help people become more productive and improve academic performance. This session will cover four steps that may help people manage time more effectively: organizing time, assessing time, setting priorities, and scheduling time (see online supplementary materials for more information).*The study cycle*: The study cycle is a 5-step approach to learning that may help students’ academic performances by reinforcing new content and making them feel more confident. This session will cover the 5 steps of the study cycle: preview, attend, review, study, and assess (see online supplementary materials for more information).

#### Structure of the control sessions

To control for non-specific aspects of the intervention, the study skills control group (developed for the present study) will mirror the structure of the Shamiri intervention. Each condition contains the same number of exercises and group discussions, within-session activities are similar in format (e.g., reading, writing, and discussion activities), and between-session take-home assignments require similar effort.

As detailed, the study skills control consists of four sessions, which are each one-hour long and 1 week apart. Take-home assignments are also assigned between sessions.

##### Session one: note-taking

During session one, group leaders will offer a didactic introduction to the 5Rs of note-taking. Then, participants will complete an exercise to practice the new note-taking method: They will read a short article about climate change and take notes using the 5Rs strategy they just learned. For homework, participants will be asked to complete three tasks: they will (1) identify one particular class during which they used the 5Rs of note-taking, (2) describe how they used the 5Rs to take notes, and (3) reflect on whether their learning improved as a result of using the new note-taking strategy.

##### Session two: effective study strategies

To begin session two, participants will reflect on the homework in a group discussion (e.g., What was rewarding or challenging about using the 5Rs? Do you plan to use them in the future?). Then, group leaders will introduce ten effective study strategies. Participants will be asked to discuss these ten strategies, examples of when they have used them, and other strategies that have worked for them. For homework, participants will be asked to complete three tasks: they will (1) identify a specific academic challenge they face over the course of the following week, (2) employ one strategy from the ten discussed in this session to address the challenge, and (3) reflect on whether their learning improved as a result of using the new strategy.

##### Session three: time management

To begin session three, participants will reflect on their homework assignment in a group discussion (e.g., Which strategies worked for you? Which ones did not? Why? What strategies might you use in the future?). Then, group leaders will introduce the concept of time management and lead a discussion about the four steps to improving it as a skill. For homework, participants will be asked to track and write down how they spend their time on activities like schoolwork, sleeping, and eating. This homework is intended to help participants understand how they are actually spending their time each day.

##### Session four: the study cycle

To begin session four, participants will reflect on their homework assignment in a group discussion. Group leaders will ask if anybody is willing to share their time management worksheet and discuss with the group. Then, group leaders will introduce the five-step study cycle and discuss it with the students. Finally, group leaders will lead a discussion about how participants can continue practicing skills they have learned from all the sessions in the future. There is no take-home activity following this fourth and last session. At this point, participants are allowed to keep the Shamiri booklet, which contains all the lessons and exercises from the four sessions of the study-skills sessions. Session four also lasted for 40 min to allow students ample time to complete endpoint assessment.

#### Intervention fidelity

We will assess intervention fidelity—including group leader adherence to protocol manual and group leader competence in delivering the Shamiri and study-skills interventions—using a fidelity rubric (see Table 2) developed by the study team. In this rubric, sessions are broken down into small 5–10-min chunks that reflect the activities which are outlined in the protocol manual. Raters will listen to and rate these chunks. They will code group leader adherence to protocol manual (i.e., whether a group a leader followed manual and delivered required content classified as 0 = no, 1 = yes) and group leader competence (i.e., effectiveness in communicating concepts and skillfulness of delivery, rated from 1 = not-competent to 5 = very competent). Ten percent of the total sessions will be assessed for fidelity.

**Table 2 Tab2:** Intervention fidelity rubric

The group leader followed the study protocol and delivered the required content	
The group leader adhered to the specifications around the content delivered (i.e., handed out necessary articles/materials, facilitated discussion)	
In your opinion, how thoroughly did the group leader deliver the required content	
In your opinion, how skillfully did the group leader deliver the required content	
In your opinion, did the group leader deliver the required content in a clear and accessible manner	

Raters (*N* = 2) will be recruited from psychology or social science departments at local universities in Nairobi. The raters will be blind to study purposes. They will first undergo a series of trainings led by the first author, including a didactic training on the protocol manuals of the Shamiri and study-skills groups, a training of the fidelity rubric, and training on the 5–10-min chunks. The raters will then listen to a randomly selected sample from each of the conditions, and rate them independently. After this, the raters will work with a member of the study team and walk through their ratings. Next, the raters will grade a randomly selected 10% of the audio-recordings of the Shamiri and study-skills sessions.

### Measures

#### Primary outcome measures

##### Patient Health Questionnaire-8

We will use the 8-item version of the Patient Health Questionnaire-9, the Patient Health Questionnaire-8, to assess youth depression symptoms. PHQ-8 scores are highly correlated with PHQ-9 scores, and the same cutoffs can be used to assess depression severity [27, 38]. The PHQ has previously been used with both Kenyan adolescents [25] and adults [39, 40].

##### Generalized Anxiety Disorder Screener-7

The Generalized Anxiety Disorder Screener-7 (GAD-7) [28] is used globally to screen for generalized anxiety disorder in adolescents and adults. The GAD-7 has previously been used with both Kenyan adolescents [25] and adults [39, 40].

### Secondary outcome measures

#### Academic performance

##### Average term grade

Academic grades of the participants will be collected for three school-terms: the school-term before the intervention (January to April 2019), the school-term during the intervention (May to August 2019), and the school-term after the intervention (September to November 2019). To determine students’ average term grade, we will calculate a mean term grade from their grades in all the subjects in which they will be enrolled. Although subject enrollment varies across different schools, students are typically expected to enroll in between 6 and 12 subjects. In order to compare students’ grades across different grade levels, academic subjects, and schools, we will convert the academic grades to standard scores (M = 60, SD = 10, chosen arbitrarily and used in rescaling); this standardization was piloted in our pilot RCT of this intervention [13].

##### Science and math score

We will calculate a science and math score for each of the three semesters for which academic grades will be collected. The score will be calculated as the mean grade of the math, biology, chemistry, and physics grades. As with the average term grade, we will convert these grades to standard scores with M = 60, SD = 10 used in rescaling.

##### Humanities and languages score

We will calculate a humanities and languages score for each of the three semesters for which academic grades will be collected. The score will be calculated as the mean grade of the English, Kiswahili, history, geography, and religious studies grades. As with the average term grade, we will convert these grades to standard scores with M = 60, SD = 10 used in rescaling.

##### Self-reported perceived academic performance

We will ask students to self-report on how they perceive their academic performance. This will be a one-item instrument that will ask them to self-report their perceived academic performance on a 5-point Likert scale from not satisfactory to excellent. The item has been used in a previous study with Kenyan university students [41].

##### Kenya Certificate of Primary Education (KCPE) scores

The KCPE is a national examination that all students take at the end of 8 years of primary school and determine admission to secondary school [24, 25]. KCPE scores will be collected for all participants, not as an outcome measure, but as a potential moderator of changes in academic performance outcomes.

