The Shamiri intervention draws upon evidence-based components of brief scalable interventions that involve non-clinical psychological principles (rather than treatment of psychopathology). Specifically, Shamiri draws on previous research on brief single-component interventions that are sometimes called “wise interventions” [14, 15], some of which have been found to improve youth mental health outcomes [16]. Wise interventions (WIs) are brief and require minimal training of lay-providers. Furthermore, they emphasize overall human functioning rather than referring to mental health disorders. Thus, wise interventions may circumvent social stigma in a way that formal psychotherapy techniques do not [16]. The specific WI components of the Shamiri protocol are growth-mindset [17–19], gratitude [20], and value affirmations [21]. The Shamiri intervention has been trialed previously with Kenyan youths. In a randomized controlled trial of the group-based Shamiri with high-symptom youths in an urban slum (*N* = 51, ages 14–17), adolescents who met a clinical cut-off for depression and anxiety were randomized into either the Shamiri intervention or an active study-skills control group; those assigned to the intervention group showed improvements in youth depression and anxiety symptoms, academic performance, and perceived social support from friends [13]. However, the trial was limited by a modest sample size and limited follow-up. Consequently, a replication of the Shamiri intervention with larger sample size is a logical next step.

This study has two primary objectives. The first is to evaluate an enhanced Shamiri group intervention—which incorporates student and stakeholder feedback from the previous Shamiri trial [13]—for depression and anxiety for youths with elevated symptoms in Kenya. The Shamiri intervention aims to be low-cost, to be positively focused in order to circumvent stigma, and will rely on empirically supported principles that can be delivered in a low-resource community setting by lay-providers. The second objective is to conduct moderator and mediator analyses on study outcomes to identify for whom and under what circumstances the treatment works.

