#### Analysis of primary and secondary study outcomes

Outcome measures will need to demonstrate internal consistency with Kenyan youths as indexed by a Cronbach’s alpha of at least 0.70 [50] to be considered for further analyses.

Our analyses will follow an intent-to-treat approach, including all participants initially randomized to an intervention condition. We will run a linear mixed-effects model comparing intervention and control groups on each primary and secondary outcome. Models will be organized to reflect the hierarchical structure of the data described earlier with crossed random effects for schools and group leaders and strict hierarchical nesting for observations in participants, participants in groups, and groups in group leaders. All models will include a random intercept that will allow for individual variation at baseline. We will include a random slope that will allow for individual variation in outcome change rates; however, should this result in overfitting (i.e., random effects structure becoming too complex to be supported by the data), we will remove the random slope to allow for more parsimonious models. Time, intervention condition, and their interaction will be included in all models. Covariates will include age (in years) and sex. Age will be included because older adolescents are reported to face increased psychosocial stress, which may exacerbate depressive and anxiety symptoms [25, 51]. Sex will be included because sex differences in internalizing problems have been documented in Kenyan adolescents [24, 25, 29, 52]. We will build two models, one which will include schools a random slope thus allowing for variation in outcome change rates by school, and another with school as a covariate because students in resource-poor schools in Kenya have reported higher anxiety symptoms than students in schools with more resources [25]. We will use Akaike Information Criterion (AIC) to determine which of the two models will be a better fit for the data. Significant (*p* < .05) condition × time interactions in predicted directions will indicate that the intervention condition produced more rapid improvements in outcomes across the full study period (baseline to 4-week endpoint), as compared to the control.

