We will calculate effect sizes (ESs) for total pre- to post-intervention change in depressive symptoms (the primary study outcome) using differences in means; these ESs will compare mean gain scores (Cohen’s *d*) reflecting changes in each outcome from baseline to post-treatment for youths in the Shamiri intervention versus study skills control intervention. Statistically significant, positive Cohen’s *d* values will indicate greater improvements for intervention group youths versus control group youths.

Participants who miss one or more intervention sessions will be permitted to attend future sessions. Missing data will be imputed as described earlier. As part of our main analyses, we do not plan to carry out additional analyses such as subgroup analyses to gauge for intervention effects on primary and secondary outcomes. However, we may later conduct additional exploratory analyses (e.g., moderator analyses) in papers separate from those reporting main and secondary trial outcomes.

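### KCPE, a pre-allocation attainment score collected for everyone, has no role in the analysis of the three grade outcomes: a minor loss of precision, not a bias

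*Protocol article*

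**What the plan says.** The section on KCPE scores describes a national examination taken at the end of primary school that determines secondary-school admission. On its use: "KCPE scores will be collected for all participants, not as an outcome measure, but as a potential moderator of changes in academic performance outcomes".

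The section on analysis of primary and secondary outcomes sets one model form for all outcomes. "Time, intervention condition, and their interaction will be included in all models", and "All models will include a random intercept that will allow for individual variation at baseline". On adjustment: "Covariates will include age (in years) and sex". School enters either with a random slope or as a covariate, and AIC decides between the two. The reasons given are psychosocial stress for age, internalizing problems for sex and anxiety symptoms for school. None concerns grades.

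For the main analyses, "we do not plan to carry out additional analyses such as subgroup analyses". The section continues: "However, we may later conduct additional exploratory analyses (e.g., moderator analyses) in papers separate from those reporting main and secondary trial outcomes". The Background had listed moderator work as an objective ("The second objective is to conduct moderator and mediator analyses on study outcomes to identify for whom and under what circumstances the treatment works"), but the analysis section leaves it optional.

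Grades are collected for three terms: "the school-term before the intervention (January to April 2019), the school-term during the intervention (May to August 2019", and September to November 2019. The average term grade is a mean over all enrolled subjects, typically 6 to 12. All three grade scores are rescaled to mean 60 and SD 10.

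**The concern.** KCPE is sat before secondary school, so it precedes allocation and treatment cannot affect it. It measures prior attainment, which is what one would expect to predict term grades. The plan collects it for everyone, yet gives it only a moderator role in analyses that may never be done. The covariates applied to the grades were chosen for depression and anxiety.

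What is at stake is the precision of three secondary outcomes. They matter to the trial's argument: the Discussion says that effects on school performance would be especially relevant where stigma limits help-seeking. No primary conclusion depends on them.

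**Working it through.** The protocol gives no figure on this point, so there is none to reproduce. It also gives no correlation between term grades or between KCPE and grades. The values below are assumptions, shown over a range.

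**Step 1. Does KCPE help in the planned model?** Let grades have unit variance and correlation r between terms, so the within-student residual variance is 1 − r. With complete data on three equally spaced terms and a participant random intercept, the condition-by-time slope rests on (third term − first term)/2 for each student. Its variance is 2(1 − r)/4. With r = .7 and 210 per arm:

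SE = √[(2 × .3/4) × (2/210)] = √(.15 × .00952) = .0378.

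KCPE does not appear in this formula, because a time-constant covariate is absorbed at the participant level. A simulation agrees (60 data sets, 420 students, three terms, r = .7, KCPE-grade correlation .5, no higher-level clustering): SE .0378 without KCPE and .0378 with it, ratio 1.000, with identical estimates to rounding. If KCPE correlates equally (k) with every term's grade, its covariance with change is k − k = 0, so a KCPE-by-time term would not help either.

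**Step 2. Does KCPE help once the model conditions on the pre-intervention grade?** Take one post-baseline term, with KCPE correlated k with both grades:

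- residual variance given the pre-grade: 1 − r²
- R² given the pre-grade and KCPE: (r² + k² − 2rk²)/(1 − k²)
- further proportional cut: x = k²(1 − r)/[(1 − k²)(1 + r)]
- equivalent participants: 420 × x/(1 − x)

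At r = .7 the pre-grade alone leaves 1 − .49 = .510:

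| k | R² with KCPE | Residual variance | Further cut | Equivalent of 420 |
|---|---|---|---|---|
| .30 | .499 | .501 | 1.7% | 7 |
| .45 | .513 | .487 | 4.5% | 20 |
| .60 | .541 | .459 | 9.9% | 46 |

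For k = .45: R² = (.49 + .2025 − 1.4 × .2025)/.7975 = .409/.7975 = .513. On the protocol's scale (SD 10), the residual SD goes from 10√.510 = 7.14 to 10√.487 = 6.98.

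For k from .30 to .60, the further cut is 2.5% to 14.1% at r = .6 and 1.1% to 6.2% at r = .8. Widening to r of .5 to .9 and k of .3 to .7 gives 0.5% to 32%. If the two later terms are averaged, the cuts at r = .7 become 2.5%, 6.3% and 14.1%.

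**Step 3. Where does the gain over the plan come from?** With one pre and one post term, a change contrast has variance 2(1 − r) = .600 at r = .7. Conditioning on the pre-grade gives .510, a cut of .090. Adding KCPE then removes .009, .023 or .051. Most of the gain therefore comes from the change of model form.

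**The case against.** The strongest reply is that nothing in the protocol is wrong here. Keeping a baseline variable for exploratory moderator work is a legitimate choice, and the KCPE section and the analysis section agree on it. Randomization leaves the comparison unbiased without KCPE. The longitudinal model already contains the pre-intervention grade, a mean over several subjects, so stable academic level is removed from the tested contrast. Within that model KCPE adds nothing.

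Most of this stands. A reader might infer that the grade outcomes are analysed with no account of prior attainment, or that omitting KCPE biases them. The documents support neither. A reader might also suppose that listing KCPE beside age and sex would sharpen the planned test; Step 1 shows that it would not. Nor do the documents say that KCPE is on a common scale for all participants. Students come from several forms, who would ordinarily have sat different years' papers, and comparability between years is not addressed.

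What the reply does not remove is narrower. The article states both KCPE's role and the covariates, so this is not simply a detail left to a fuller document. The covariates have no stated rationale for grades. The figures in Step 2 are already net of the pre-intervention grade, so a positive, though possibly very small, gain remains under the alternative model.

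**Conclusion.** The point holds as a minor efficiency suggestion on three secondary outcomes. Beyond the pre-intervention grade, KCPE would lower residual variance by about 1% to 14% for a single post-baseline term, or roughly 2% to 10% at r = .7.

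This rests on assumed correlations and on KCPE relating equally to pre- and post-intervention grades. KCPE determines admission, so its spread within a school may be narrow, which makes the low end plausible. The conversion to participants ignores clustering by group, leader and school and is only a scale for the gain. The percentages measure improvement over a baseline-conditioned model that the protocol does not specify; they are not a loss within the planned condition-by-time model.

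**What to change.** For average term grade, science and math, and humanities and languages, analyse the post-baseline term grades in a model that conditions on the January to April 2019 grade and includes KCPE as a covariate. Keep the clustering terms and the existing covariates. Leave KCPE's exploratory moderator use as it is; adjustment does not prevent it.

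The protocol gives the trial status as completed, so for this trial the analysis should be reported as supplementary and labelled as such. A successor protocol could pre-specify it. If examination years differ, say how the scores are made comparable, for example by standardizing within year.

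The cost is more than one added covariate: the model form changes for three secondary outcomes, and missing KCPE values must be added to the imputation. No new data collection is needed.
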